**Methods:**

A total of 81 stroke patients will be recruited and randomly assigned to control, fixed reward, or probabilistic reward groups at a ratio of 1:1:1 using a randomized number table method. Participants will undergo 10 days of daily hand motor function rehabilitation training, with sessions lasting 20 min each. The training will involve pegboard tests and box and block tests. Control group participants will receive standard training, while fixed reward group members will receive monetary incentives for completing tests, and probabilistic reward group members will have the chance to win monetary rewards through a lottery box. Rehabilitation motivation and motor performance and functional near-infrared spectroscopy brain imaging will be conducted at designated time points. The primary outcome measure is the stroke rehabilitation motivation scale, and the second outcome measures include motor performance, simple test for evaluating hand function, motivation and pleasure scale self-report, and Pittsburgh rehabilitation participation scale.

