**Figure 1 fig1:**
[figure not shown]
Flowchart of study design. BBT, Box and Block Test; fNIRS, Functional Near-Infrared Spectroscopy; MAP-SR, Motivation and Pleasure Scale Self-Report; PRPS, Pittsburgh Rehabilitation Participation Scale; SRMS, Stroke Rehabilitation Motivation Scale; STEF, Simple Test for Evaluating Hand Function.

**Inclusion Criteria**: (1) Patients diagnosed with stroke based on clinical assessment and comprehensive imaging examinations. First onset of stroke; duration of illness ≥1 month. (2) The impairment of motor function in the right upper limb (including the forearm and hand). (3) Age between 18 and 80 years, irrespective of gender, and right-handed. (4) Brunnstrom stages III to V. (5) Able to tolerate assessment sessions lasting from half an hour to one hour. (6) Participants and their legally authorized guardians understand and agree to participate in this study, and jointly sign the informed consent form.

**Exclusion Criteria**: (1) Patients with severe systemic diseases such as cardiopulmonary disorders, uremia or heart failure that render them unable to tolerate rehabilitation treatment. (2) Diagnosed with psychiatric disorders, severe depression, or having a family history of psychiatric disorders (HAMD-17 scores > 24). (3) Severe joint contractures (active range of motion of the upper limb is less than half of the normal range without eliciting pain). (4) Presence of consciousness disorders due to any cause, Glasgow coma score < 15 (14). (5) Auditory or visual impairments that may affect assessment and treatment. (6) Use of medications altering cortical excitability (antiepileptic drugs, sedatives, etc.). (7) Significant pain or mental disorders (visual analog scale > 6).

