### Sample size

The statistical software G-power (Heinrich Heine University Düsseldorf, Dusseldorf, Germany) was utilized to ascertain the sample size, with an alpha value set at 0.05, power at 0.95. By employing Cohen’s d using data extracted from a prior study by Chen et al. (15), we ascertain the mean discrepancy between groups to be 2.34 (27.54–25.2), with a pooled standard deviation approximating 3.47. Acknowledging the discrepancy in sample sizes between the two groups, the effect size is computed to be 0.674. With these parameters, the calculated sample size per group was determined to be 23 participants, summing up to 69 participants across three groups. Anticipating a dropout rate of 15%, the final sample size was adjusted, necessitating 27 participants per group, resulting in a total sample size of 81 participants.

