### Randomization, allocation, and blinding

The randomization procedure employed in this study adhered to rigorous standards, utilizing a randomized number table method. Subjects were allocated randomly into three groups (control group, fixed reward group and probabilistic reward group) at a precise ratio of 1:1:1, ensuring that each group consisted of 27 participants. Group allocation was meticulously executed using the sealed envelope method. Prior to participant assignment, random allocation sequences were meticulously generated and securely housed within sequentially coded, sealed, opaque envelopes. Following confirmation of subject eligibility by the researcher, envelopes were systematically unsealed, and subjects were then allocated to their respective groups.

In adherence to stringent confidentiality protocols, prior to envelope unsealing, the names and comprehensive profiles of eligible subjects were meticulously transcribed onto the exterior of each envelope. Duplicate records were also securely enclosed within, serving as a safeguard against any potential data loss or discrepancies. Furthermore, to ensure the utmost confidentiality and integrity of the allocation process, each envelope was reinforced with an additional layer of protection, such as a hardboard or tin foil insert, effectively shielding its contents from visibility under intense lighting conditions.

To uphold the scientific rigor of the study and mitigate the risk of bias, a single-blinding approach was meticulously implemented. This method ensured that assessors remained blinded to the subjects’ group allocations and the specific intervention protocols administered. Moreover, to maintain consistency and objectivity in the evaluation process, all patient training sessions and subsequent assessments were meticulously recorded. These assessments were conducted by therapists who were intentionally kept unaware of the patients’ group assignments. In case of anomalous data detected during data analysis or data verification, the designated data analyst will promptly notify both the principal investigator and the assessor. Subsequently, a comprehensive review of the recorded sessions will be conducted to verify the accuracy and reliability of the obtained results, thereby upholding the highest standards of scientific integrity and validity.

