### Outcome assessment

The components of the assessment include basic information (gender, age, duration of illness, medication history, etc.), motivation, motor performance and objective assessments. The main assessments focus on motivation and motor performance. Comprehensive video recordings of each training session will be subjected to meticulous analysis to evaluate daily motor performance. Rehabilitation motivation evaluations and functional near-infrared spectroscopy (fNIRS) measurements will be conducted at designated time points (Table 1).

**Table 1 tab1:** Recommended content for the schedule of enrolment, interventions, and assessments.

	Study period						
	Enrolment and assessment	Allocation	Training			Follow-up	
Timepoint	−D_1_	0	D_1_	D_2_–D_9_	D_10_	D_14_	D_28_
Enrolment							
Eligibility screen	X						
Informed consent	X						
Allocation		X					
Interventions							
Control group							
Fixed reward group							
Probabilistic reward group							
Assessments							
SRMS	X		X		X	X	X
MAP-SR	X		X		X	X	X
PRPS	X		X		X	X	X
Motor performance	X		X	X	X	X	X
fNIRS	X		X		X	X	X

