### Statistical analysis

Categorical variables like gender and affected side will be presented as percentages and compared using the chi-square test. Continuous variables will undergo normality assessment with the Shapiro–Wilk test and variance homogeneity examination with Levene’s test. One-Way ANOVA will compare motivation among groups before and after training, followed by Tukey’s HSD test for *post hoc* comparisons. The repeated measures ANOVA was performed to analyze changes in rehabilitation motivation scales data and average time spent in pegboard test and BBT in the three groups. Non-normal or heterogeneous data will be analyzed using the Kruskal-Wallis test, with *post hoc* tests conducted using Dunn’s test. Normal data will be presented as mean ± standard deviation, while non-normal data will be presented as median and quartiles. The significance level (P) for hypothesis testing will be set at 0.05.

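### The after-training one-way ANOVA of motivation uses neither the pre-training scores nor the screening HAMD-17, which gives up precision without causing bias

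*Protocol article*

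**What the plan says.** The abstract fixes the outcome: "The primary outcome measure is the stroke rehabilitation motivation scale". Table 1 places SRMS and MAP-SR at the enrolment assessment, on D1 and D10, and at follow-up on D14 and D28, so both have a pre-training value.

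The Statistical analysis section gives two parametric analyses of motivation:
- "One-Way ANOVA will compare motivation among groups before and after training", followed by Tukey's HSD;
- "The repeated measures ANOVA was performed to analyze changes in rehabilitation motivation scales data".

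Kruskal-Wallis with Dunn's test is the fallback for non-normal or heterogeneous data. None of these carries a covariate.

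HAMD-17 appears once, in exclusion criterion (2): "Diagnosed with psychiatric disorders, severe depression, or having a family history of psychiatric disorders (HAMD-17 scores > 24". It is not among the baseline items that the Outcome assessment section names: "The components of the assessment include basic information (gender, age, duration of illness, medication history, etc.), motivation, motor performance and objective assessments". Allocation is "at a precise ratio of 1:1:1, ensuring that each group consisted of 27 participants", and no stratification factor is named.

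**The concern.** A one-way ANOVA of after-training SRMS compares raw group means. Stable differences between patients in motivation stay in its error term, although the trial measures them before training. Running the same test on the pre-training scores does not help: it describes the arms at baseline but does not bring the baseline value into the later comparison.

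Depression severity is a plausible second prognostic variable. The outcomes are self-reported motivation (SRMS) and motivation and pleasure (MAP-SR), and a HAMD-17 score of 24 or below does not by itself exclude a patient. The stated analysis does not use that score either.

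What is at stake is the width of the confidence intervals and the power of the between-arm comparisons, in a trial whose power on a simple two-arm test is well below the planned value.

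**Working it through.** **Inputs from the Sample size section.** "with an alpha value set at 0.05, power at 0.95"; "we ascertain the mean discrepancy between groups to be 2.34 (27.54–25.2), with a pooled standard deviation approximating 3.47"; effect size 0.674; 23 per group before dropout and 27 after. The sidedness of alpha is not stated; two-sided is used here.

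**The plan's own figures first.** d = 2.34/3.47 = 0.674, which reproduces. The 23 per group does not: a two-sided two-sample t test at d = 0.674 needs 59 per group for 95% power. With 23 per group its power is 0.61 (noncentral t). That is a separate problem; it is used here only as the starting point.

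**Assumed inputs.** The documents give no correlation between baseline and later SRMS, or between HAMD-17 and SRMS. Assumed magnitudes:
- baseline with outcome, r_b = 0.5 to 0.7;
- HAMD-17 with outcome, r_h = 0.3 to 0.4;
- HAMD-17 with baseline SRMS, r_bh = 0.3 to 0.4.

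**Step 1: baseline score only.** Residual SD = SD × √(1 − r_b²), so the effective d is 0.674/√(1 − r_b²). The one or two degrees of freedom spent are ignored.

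| r_b | Variance removed | Effective d | Power, 23 per group |
|---|---|---|---|
| none | 0% | 0.674 | 0.61 |
| 0.5 | 25% | 0.674/0.866 = 0.779 | 0.73 |
| 0.6 | 36% | 0.674/0.800 = 0.843 | 0.80 |
| 0.7 | 49% | 0.674/0.714 = 0.944 | 0.88 |

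**Step 2: add HAMD-17.** R² = (r_b² + r_h² − 2·r_b·r_h·r_bh)/(1 − r_bh²). Further residual variance removed = 1 − (1 − R²)/(1 − r_b²).
- Most favourable case (r_b = 0.5, r_h = 0.4, r_bh = 0.3): R² = (0.25 + 0.16 − 0.12)/0.91 = 0.319. Further reduction = 1 − 0.681/0.75 = 9%. Power goes from 0.73 to 0.77.
- Least favourable case (r_b = 0.7, r_h = 0.3, r_bh = 0.4): R² = (0.49 + 0.09 − 0.168)/0.84 = 0.490. Further reduction is about 0.1%. Power stays at 0.88.

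So HAMD-17 adds 0 to 4 percentage points beyond the baseline score.

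**Step 3: HAMD-17 alone, no baseline score.** At a HAMD-17/SRMS correlation of 0.2, 0.3 and 0.4, variance falls by 4%, 9% and 16%, and power at 23 per group goes from 0.61 to 0.63, 0.65 and 0.68. These figures apply only to a model without baseline SRMS and cannot be added to those in Step 1.

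**Step 4: chance imbalance in HAMD-17.** With 27 per arm, the difference between two arm means has SD √(2/27) = 0.27 HAMD-17 SDs. A given pair differs by more than 0.3 SD with probability 27%; at least one of the three pairs does so with probability 51%. A 0.3 SD gap moves the SRMS contrast by 0.3 × 0.2 = 0.06 to 0.3 × 0.4 = 0.12 SD. The standard error of that contrast is also 0.27 SD, so the shift is under half a standard error.

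**The case against.** The strongest case against is that nothing here is invalid. Unadjusted ANOVA after randomisation is a legitimate analysis, and an article often leaves secondary covariates to the analysis plan. The first half stands. The second does not dispose of the point, because the article does not leave the method open: it names the test for motivation, and that test ignores a baseline value that the schedule collects.

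The repeated measures ANOVA is a fair counter. It includes pre-training SRMS and so already absorbs part of the stable differences between patients. The gain in Step 1 is therefore measured against the one-way ANOVA, not against everything in the section.

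Several stronger readings are tempting, and the documents do not support them:
- *Depression imbalance biases the primary comparison.* Chance imbalance under randomisation is not bias, and the ANOVA standard error already reflects it.
- *Every patient has a HAMD-17 score.* This is a reasonable inference from a numeric cut-off, but Table 1 shows only an eligibility screen, and the list of baseline items is open-ended.
- *All patients from no depression up to a score of 24 enter.* The same criterion also lists diagnosed psychiatric disorders and family history. The enrolled range may be narrower, which would weaken any correlation.
- *HAMD-17 lifts power from 61% to as much as 68%.* That holds only if baseline SRMS is left out of the model.
- *Adjustment deals with depression changing how patients respond to rewards.* That is effect modification, which a main-effect covariate does not model.

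**Conclusion.** The point holds as a matter of efficiency. The stated after-training one-way ANOVA of SRMS and MAP-SR discards pre-training scores that Table 1 collects. Most of the recoverable precision lies there: power rises from 0.61 to about 0.73 to 0.88 for a two-arm comparison at 23 per group. HAMD-17 is a minor addition, removing 0 to 9% of the remaining residual variance.

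These sizes rest on the assumed correlations, on d = 0.674 applying to SRMS, and on a single two-sided 0.05 comparison without Tukey's correction. Type I error is not affected. Adjustment does not repair the sample size either: even at r_b = 0.7 (effective d = 0.944), 95% power needs 31 per group, against the 23 stated.

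**What to change.** In the Statistical analysis section, replace the after-training one-way ANOVA of SRMS and MAP-SR with a pre-specified ANCOVA, or a mixed model over the scheduled visits, that adjusts for the baseline score of the same outcome. Where the screening HAMD-17 score is recorded for all patients, it may be added as a second continuous covariate; if so, say that it is kept in the case report form. Name the covariates before the data are unblinded, so that they are not chosen in response to an observed imbalance.

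The cost is a sentence or two of text and one or two degrees of freedom. The baseline scores are already scheduled, so the main change needs no further visit, assessment or patient. The HAMD-17 part is optional, and it is free only if every patient is in fact scored at screening.

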### Sample size

The statistical software G-power (Heinrich Heine University Düsseldorf, Dusseldorf, Germany) was utilized to ascertain the sample size, with an alpha value set at 0.05, power at 0.95. By employing Cohen’s d using data extracted from a prior study by Chen et al. (15), we ascertain the mean discrepancy between groups to be 2.34 (27.54–25.2), with a pooled standard deviation approximating 3.47. Acknowledging the discrepancy in sample sizes between the two groups, the effect size is computed to be 0.674. With these parameters, the calculated sample size per group was determined to be 23 participants, summing up to 69 participants across three groups. Anticipating a dropout rate of 15%, the final sample size was adjusted, necessitating 27 participants per group, resulting in a total sample size of 81 participants.

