Previous studies have explored the effectiveness of fixed reward-based training in stroke rehabilitation, but there remains a need for comparative research to determine which approach—fixed or probabilistic reward—is more sensitive and efficient. The optimal types and delivery methods of rewards in stroke rehabilitation remain underexplored. Addressing this gap in the literature will provide valuable insights into optimizing stroke rehabilitation protocols and ultimately improving patient outcomes. This study aims to compare the efficacy of fixed and probabilistic reward strategies in enhancing motor learning ability and rehabilitation motivation in stroke patients, and seeks to inform the development of evidence-based rehabilitation protocols and improve patient outcomes following stroke.

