### Primary outcomes

The Stroke Rehabilitation Motivation Scale (SRMS) is a validated assessment tool developed by Australian scholar White in 2012, specifically tailored to measure the motivation levels of stroke patients engaging in rehabilitation programs (16). It offers a structured approach to evaluate various dimensions of motivation essential for effective rehabilitation. The scale comprises seven dimensions, including amotivation, external regulation, introjected regulation, identified regulation, integrated regulation, intrinsic motivation to know, and intrinsic motivation to accomplish. Each dimension represents different aspects of motivation, ranging from external factors like rewards or obligations to internal factors such as inherent satisfaction and personal goals. It consists of 28 items, including both positively and negatively phrased statements, allowing for a nuanced assessment of motivation levels. The SRMS serves as a valuable tool in rehabilitation practice, enabling clinicians to assess, monitor, and address motivational barriers to maximize the effectiveness of stroke rehabilitation programs.

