Earlier studies demonstrated that reward alone did not enhance the learning rate in the VMR task, whereas reward combined with punishment not only accelerated the learning rate but also increased the learning extent (28, 29). Nikooyan et al. suggested that reward feedback alone can drive motor adaptation (without increasing the rate beyond that of the control group), and the combination of reward and sensory feedback accelerates learning (30). It was also supported that reward alone boosts or accelerates learning speed in sequence learning paradigms. The participants with monetary incentives have a higher learning rate in a discrete motor sequence task because the reward enhances motivation (31). Additionally, Sebastian Sporn et al. dissociated the effects of different types of rewards, namely, performance feedback and monetary incentives, through a novel motor task, and the results demonstrated that monetary incentives alone rapidly shortened movement time, whereas feedback after correct responses primarily improved learning-related movement time performance. Importantly, pairing both monetary incentives and feedback after correct responses enhanced movement time performance and improved fusion of movements (12). The majority of studies investigating the impact of rewards on motor learning mentioned above were conducted in healthy participants, employing fixed reward paradigms. It wasn’t until 2017 that, in a visuomotor rotation-based reaching task utilizing a robotic arm, the reward group of chronic stroke patients exhibited superior adaptation and readaptation compared to the neutral group, and finally, the reward group showed greater retention. Quattrocchi et al. were the first to provide evidence that reward and punishment can augment motor adaptation in stroke patients (32). This finding was corroborated by a recent study which was also conducted in stroke patients (33). However, the rewards utilized in these investigations remained fixed. To date, there is still a lack of randomized controlled trials examining the effects of fixed versus probabilistic rewards on motor rehabilitation in stroke patients. The study we are undertaking aims to address this gap.

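### The stated 95% power rests on one two-group effect (d = 0.674) that is not tied to any contrast or outcome, and it does not hold for fixed versus probabilistic reward

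*Protocol article*

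**What the plan says.** The Sample size section sets its targets as follows: "with an alpha value set at 0.05, power at 0.95". The effect comes from one earlier study ("By employing Cohen’s d using data extracted from a prior study"), for which "we ascertain the mean discrepancy between groups to be 2.34 (27.54–25.2), with a pooled standard deviation approximating 3.47". It continues: "Acknowledging the discrepancy in sample sizes between the two groups, the effect size is computed to be 0.674". From this, "the calculated sample size per group was determined to be 23 participants, summing up to 69 participants across three groups". An allowance for 15% dropout raises the number to 27 per group, 81 in all.

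The section does not describe the earlier study's arms, outcome or population. It does not say which of the three contrasts (fixed versus control, probabilistic versus control, fixed versus probabilistic) the effect represents.

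The Introduction gives the aim: "This study aims to compare the efficacy of fixed and probabilistic reward strategies". The Discussion places the trial's novelty in that same direct comparison, and says of the existing evidence: "To date, there is still a lack of randomized controlled trials examining the effects of fixed versus probabilistic rewards on motor rehabilitation". The Statistical analysis section plans a one-way ANOVA across the three groups, followed by Tukey's HSD for the pairs.

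**The concern.** A power statement has meaning only for a named contrast on a named outcome. Here one standardised difference between two groups is applied to a three-arm trial with no such link. The comparison that the article puts forward as its reason for being is between two active arms, and by the article's own account randomised evidence on it in stroke is lacking. The source of 0.674 is therefore unlikely to be that comparison.

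This is more than a labelling gap. A reader of the Sample size section would conclude that the trial has a 95% chance of detecting the planned difference between the two reward strategies. If the design lacks that property, the main comparison has been given a precision it does not have. The planning effect and its target power are stated in the article as settled, so they are not a detail left to a later analysis plan.

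**Working it through.** **Inputs.** From Sample size: mean difference 27.54 − 25.2 = 2.34; pooled SD 3.47; alpha 0.05 (sidedness not stated, taken as two-sided, with one-sided also shown); power 0.95; 23 per group before dropout; 15% dropout. From Statistical analysis: three groups, Tukey's HSD for pairs.

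**Step 1, the effect size.** d = 2.34 / 3.47 = 0.674. This reproduces.

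**Step 2, the n per group.** For two means, n = 2(z₁₋α/₂ + z₁₋β)² / d² = 2(1.960 + 1.645)² / 0.674² = 57.2, so 58 per group. The noncentral t gives 59. One-sided, the two figures are 48 and 49. The stated 23 does not reproduce.

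Other readings of the same inputs do not give 23 either:

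| Reading | n per group for 95% power |
|---|---|
| Three-group ANOVA, 0.674 entered as Cohen's f | 13 |
| Three-group ANOVA, f = d/2 = 0.337 | 47 |
| Three-group ANOVA, one group differs by d (f = 0.318) | 53 |
| Three-group ANOVA, middle group halfway (f = 0.275) | 70 |
| One-sample or paired t-test | 31 two-sided, 26 one-sided (total n) |

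Repeated-measures variants with 2 to 5 time points and an assumed correlation of 0.5 gave no total of 69.

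**Step 3, the dropout allowance.** 23 × 1.15 = 26.5, rounded up to 27, which matches the stated figure. Dividing by 0.85 gives 27.06, so 28. In the other direction, 27 × 0.85 = 22.95, so about 23 evaluable per arm is the right basis for what follows.

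**Step 4, power for fixed versus probabilistic reward with 23 per arm, two-sided 0.05.** The noncentrality is d√(n/2) = d√11.5, which is 2.29 at d = 0.674. The unadjusted two-sample t-test has critical value t(0.975, 44) = 2.015. Tukey's test for three groups with 66 degrees of freedom has critical value 3.391/√2 = 2.398. The article gives no effect for this contrast, so values of d below 0.674 are assumptions that show a range.

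| True gap (SD) | Unadjusted t | Tukey |
|---|---|---|
| 0.674 | 61% | 46% |
| 0.5 | 38% | 25% |
| 0.337 (half of 0.674) | 20% | 11% |

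If nobody drops out (27 per arm), power at 0.674 is 68% unadjusted and 54% under Tukey. A one-sided unadjusted test at 23 per arm reaches 73%.

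**Step 5, what 23 per arm can detect.** The standard error of a difference is √(2/23) = 0.295 SD.

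| | Unadjusted t | Tukey |
|---|---|---|
| Detectable gap, 80% power | 0.84 SD | 0.96 SD |
| Detectable gap, 95% power | 1.09 SD | 1.20 SD |
| 95% CI half-width | 2.015 × 0.295 = 0.59 SD | 2.398 × 0.295 = 0.71 SD |

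**The case against.** The strongest reply is that the source of 0.674 is not described, so nobody working from the article can say that it is the wrong contrast. That stands. A reader might infer from the Discussion that the earlier study cannot have compared fixed with probabilistic reward. The text does not go that far: it speaks of a lack of randomised trials in stroke motor rehabilitation, which leaves open a non-randomised study or one in another population. What the text supports is that the effect is not shown to be for this contrast and is unlikely to be.

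Three other inferences should also be resisted.

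- That the means of 27.54 and 25.2 cannot be scores on the Stroke Rehabilitation Motivation Scale. The article says of the scale "It consists of 28 items, including both positively and negatively phrased statements" but gives no scoring rule, so no floor or expected SD can be derived.
- That probabilistic reward would have to add a second full 0.674 SD on top of fixed reward. This needs 0.674 to be reward versus no reward, which is nowhere stated.
- That a non-significant result will be taken as equivalence. No sentence says how such a result will be read, and rules for this commonly sit in the analysis plan.

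It can also be objected that the more basic error is the 23 per group itself, and that calling the 95% inapplicable to the main question suggests that it is valid for some other one. It is not valid for any pair at d = 0.674. But correcting n alone would not settle the matter, because 59 per group would be justified only for whatever the earlier study compared.

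**Conclusion.** The point holds in this form: the stated 95% power is not a property of the design for fixed versus probabilistic reward. Even if the full 0.674 SD applies to that pair, power with 23 evaluable per arm is 61% unadjusted and 46% under the planned Tukey comparison. A smaller gap lowers it further. The 20% and 11% at half the effect are illustrations, not estimates.

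The results assume a two-sided 0.05 level, normal data with equal variances, about 23 evaluable patients per arm, and a single comparison of group means without baseline adjustment. A one-sided test or full retention raises the figures but does not bring them near 95%. The finding does not depend on knowing what the earlier study compared. It depends on the article not saying so, and on the arithmetic.

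**What to change.** Keep the 81 patients and rewrite the Sample size section.

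1. Name the contrast, outcome and population that 27.54, 25.2 and 3.47 come from, and say which of this trial's contrasts they are meant to inform.
2. Withdraw the 95% power claim for fixed versus probabilistic reward. State instead what 23 evaluable patients per arm can detect under the planned Tukey comparison: about 0.96 SD at 80% power and 1.20 SD at 95%, with a 95% CI half-width of about 0.71 SD. The unadjusted counterparts (0.84, 1.09 and 0.59 SD) can be given alongside, labelled as such.
3. Correct or remove the statement that 23 per group follows from d = 0.674 at 95% power.

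The cost is wording only, with no extra patients and no change to conduct. The downside is that the stated power becomes less favourable. If the sponsor prefers to keep 95% power for this comparison, it needs a justified effect for it and a new sample size: for an unadjusted two-sided test before dropout, 58 to 59 per arm at 0.674 SD, 104 at 0.5 SD and 229 at 0.337 SD.
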